### Sample size estimation

The sample size calculation was based on the results of Endres et al. [17]. The study was powered to detect a small interaction effect of time × intervention dose (*f* = 0.15) for the primary endpoint (α = 0.05) with a power of 80% in a variance analysis with five repeat measurements and four study groups. With these targets, 20 patients per study group were required for analysis. Assuming a dropout rate of 20% over the course of the trial, 24 patients must be included in each study group; thus, recruitment of 96 participants is required. The sample size calculation was performed using the G*Power 3 software.

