## Methods/design

### Study design

The proposed study is a randomized controlled prospective trial with four balanced treatment arms. It will compare the efficacy of two distinct non-pharmacological treatment modalities (acupuncture vs. MTT), as monotherapies and in combination, with usual care according to IHS criteria for the treatment of common episodic and chronic tension-type headaches. Usual care is the control modality. Subjects will be assigned to one of the four treatment arms (usual care, acupuncture, MTT, and MTT plus acupuncture), using pre-generated randomization lists in a ratio of 1:1:1:1 with varying permutation block sizes. The randomization scheme was prepared by a scientific colleague who is not involved in scheduling, treatment, or evaluation. After the randomization list had been created, written allocation sheets were delivered to the treating physicians in sealed opaque envelopes.

The study is headed by the first and last authors as well as the head of the Departement of Rehabilitation medicine of the Hannover Medical School (CG). Protocol decisions were made in a peer process involving all co-authors. Changes to the study protocol can be made only with the written consent of the ethics committee.

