### Outcome measurements

#### Primary outcome

To test the primary null hypothesis, the change in mean pain intensity (numerical rating scale) before the start of the intervention (T1) compared with the pain intensity 6 weeks after the end of the intervention (T3) is used as the primary endpoint.

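### The stated 80% power belongs to a five-visit interaction test; it is not established for the declared primary endpoint, the T1–T3 change in pain intensity

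*Protocol article*

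**What the plan says.** Three sections of the protocol article bear on this.

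- **Sample size estimation.** The target is an interaction: "The study was powered to detect a small interaction effect of time × intervention dose (*f* = 0.15"). It is claimed "for the primary endpoint (α = 0.05"), and the calculation is made "with a power of 80% in a variance analysis with five repeat measurements and four study groups". The result is that "20 patients per study group were required for analysis", so 80 in all, raised to 96 for dropout. G*Power 3 is named; rho and epsilon are not given.
- **Primary outcome.** The endpoint is the change in mean pain intensity on a numerical rating scale: the value before the intervention (T1) "compared with the pain intensity 6 weeks after the end of the intervention (T3) is used as the primary endpoint". That uses two visits.
- **Statistical analysis.** The primary hypothesis is tested by the time × intervention interaction in a repeated-measures ANOVA, on an intention-to-treat basis with multiple imputation. The visits in that ANOVA are not specified.

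**The concern.** The power figure and the endpoint it is attached to describe different tests. With four groups and five visits the interaction has (4 − 1)(5 − 1) = 12 degrees of freedom, and it can be significant because the groups diverge at any visit. With T1 and T3 alone it has (4 − 1)(2 − 1) = 3 degrees of freedom, uses two values per patient, and equals a one-way comparison of change scores.

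At stake is how the primary result is read. A non-significant T1–T3 comparison would be interpreted against a design power of 80%, and nothing in the article shows that this comparison has it. Conversely, if the five-visit test is the one reported, a significant result need not concern the T1–T3 change at all.

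**Working it through.** **Inputs from the article.** k = 4 groups in equal allocation, alpha = 0.05, f = 0.15, N = 80 evaluable (96 recruited), m = 5 visits in the calculation and m = 2 in the endpoint. **Assumed, because not stated:** rho and epsilon.

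**Formula** (noncentral F, within-between interaction as G*Power parameterises it):
- lambda = f² · N · m · epsilon / (1 − rho)
- df1 = (k − 1)(m − 1) · epsilon
- df2 = (N − k)(m − 1) · epsilon

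With two visits epsilon is necessarily 1.

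**Step 1: reproduce the plan's figure.** m = 5, rho = 0.5, epsilon = 1:
- lambda = 0.0225 × 80 × 5 / 0.5 = 18.0
- df = 12 and 304
- power = 80.2%, and 80 is the smallest N reaching 80%

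The stated 20 per group is reproduced.

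**Step 2: the declared endpoint, same inputs, m = 2.**
- lambda = 0.0225 × 80 × 2 / 0.5 = 7.2
- df = 3 and 76
- power = 57.9%

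With all 96 analysed, lambda = 8.64, df = 3 and 92, power = 67.1%. At N = 80, 80% power needs f ≈ 0.19. At f = 0.15 it needs 126 evaluable patients (128 in balanced arms).

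**Step 3: other rho and epsilon that also return 80.** Rho = 0.5 with sphericity is the simplest pair but not the only one.

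| rho | epsilon | five-visit power, N = 80 | T1–T3 power, N = 80, f = 0.15 |
|---|---|---|---|
| 0.50 | 1.00 | 80.2% | 58% |
| 0.54 | 0.90 | 81% | 62% |
| 0.57 | 0.80 | 80% | 65% |
| 0.60 | 0.75 | 81.8% | 69% |
| 0.65 | 0.60 | 81.1% | 75% |
| 0.69 | 0.50 | 81% | 80% |

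The two tests reach the same power only near the last row.

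Varying rho alone at m = 2, N = 80, f = 0.15 gives 43% (rho 0.3), 50% (0.4), 58% (0.5), 69% (0.6) and 82% (0.7). With epsilon = 1, values of rho other than about 0.5 do not return the stated N: the five-visit requirement is 96 at rho 0.4 and 65 at rho 0.6.

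**Step 4: f over five visits is not f over two.** Suppose the group differences follow a common profile p over T0 to T4, and the five-visit f is held at 0.15. Then

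f²(T1–T3) = 0.15² × [(p at T3 − p at T1) / 2]² / variance of p over the five visits.

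With rho = 0.5, epsilon = 1, N = 80:

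| Profile T0, T1, T2, T3, T4 | variance of p | f for T1–T3 | power |
|---|---|---|---|
| 0, 0, 1, ½, ½ | 0.14 | 0.100 | 28% |
| 0, 0, 1, 1, 1 | 0.24 | 0.153 | 60% |
| 0, 0, ½, 1, 1 | 0.20 | 0.168 | 69% |
| 0, 0, 0, 1, 0 | 0.16 | 0.188 | 79% |
| 0, 0, ½, 1, ½ | 0.14 | 0.200 | 85% |

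Example, second row: 0.0225 × 0.25 / 0.24 = 0.02344, whose square root is 0.153. The article states no profile; these are illustrations.

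**The case against.** **The calculation is correct for the test it describes.** This stands. The 20 per group reproduces, so a reader who infers an arithmetic error here would be mistaken. The fault is that the result is assigned to an endpoint the calculation does not represent.

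**The analysis may use all five visits.** The Statistical analysis section does not restrict the ANOVA to T1 and T3. If every visit enters, 80% is the right figure for that test. But that test does not address the T1–T3 change, so the mismatch moves from the sample size section to the endpoint definition and does not disappear.

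**Rho and epsilon may be given in the full protocol.** Possible, and their absence from an article is not the criticism. It does limit what can be concluded: a reader might infer that the true power is 58%, but that is one value among several compatible with the stated sample size.

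**The effect may be concentrated at T3.** Also fair. A profile that peaks at T3 and is half present at T2 and T4 gives 85%, so it cannot be said that power for the endpoint must be below 80%. The article gives no such argument.

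**It is a pilot, and recruitment is complete.** Both are true, and both argue against changing the sample size. Neither removes a formal 80% claim tied to superiority hypotheses.

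A further tempting reading is to quote low power for the pairwise comparisons in the primary hypothesis. The article sets no Bonferroni rule between arms; its correction applies to post hoc intragroup tests. Any figure at 0.05/5 would therefore rest on a rule the document does not contain.

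**Conclusion.** The point holds: 80% power is not established for the declared primary endpoint. At f = 0.15, rho = 0.5 and epsilon = 1, the five-visit interaction has 80.2% and the T1–T3 comparison about 58% with 80 evaluable patients. The 67% for 96 is an upper case, since it needs complete data from everyone recruited. Other rho and epsilon pairs that return the same N give about 62–75%, with parity near rho = 0.69 and epsilon = 0.5. If the five-visit f is fixed instead, the illustrated effect profiles span about 28% to 85%.

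The mismatch between sections is certain because it can be read from the text. The size of the shortfall depends on rho, epsilon and the time course of the effect, none of which the article states.

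**What to change.** Keep the sample size. Reconcile the three sections in this order:

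1. **Primary outcome and Statistical analysis:** state that the primary test is the group comparison of the T1–T3 change (time × group restricted to T1 and T3), with the five-visit interaction as supportive.
2. **Sample size estimation:** attribute the 80% to the five-visit interaction and declare the rho and epsilon actually entered in G*Power.
3. **Same section:** give the power of the T1–T3 test under those declared values, with a range over rho. If they were rho = 0.5 and epsilon = 1, this is about 58% at f = 0.15, and 80% at f ≈ 0.19. The sponsor should confirm the inputs first and not adopt the values inferred here.

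Do not add pairwise detectable effects at 0.05/5.

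The cost is wording, and a stated power that looks less favourable. No extra patients are needed.

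### The dropout allowance is miscalculated: 24 per group with 20% loss leaves 19.2, not the 20 required; 20% loss needs 25 per group, or 96 in total allows for 16.7%

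*Protocol article*

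**What the plan says.** All the relevant figures stand in the protocol article under Sample size estimation. The target is an interaction of time and intervention with f = 0.15, at α = 0.05, "with a power of 80% in a variance analysis"; the model is a "variance analysis with five repeat measurements and four study groups". From this the authors conclude that "20 patients per study group were required for analysis". The dropout step follows: "Assuming a dropout rate of 20% over the course of the trial, 24 patients must be included in each study group", which gives a recruitment target of 96. The Abstract repeats 24 per arm, and Study design gives equal allocation to the four arms. The article contains no other dropout rate and no rounding rule.

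**The concern.** The section makes three statements about each group: 20 are needed at analysis, 20% will be lost, and 24 are to be enrolled. Any two of them fix the third, and the third does not come out as stated. A dropout rate over the course of the trial is a fraction of those enrolled, so the required number has to be divided by 0.80. The 24 is what results when the 20% is instead added to the number of completers.

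At stake is whether the planned enrolment delivers the stated power at the dropout rate the authors themselves assume. On the article's own figures it falls slightly short. The sentence is also likely to be carried into the results report as the justification for the sample size.

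**Working it through.** **Inputs, all from Sample size estimation:** 20 analysable per group; 4 groups, so 80 in total; dropout d = 0.20; enrolled 24 per group, 96 in total; f = 0.15; α = 0.05; power 80%; m = 5 measurements.

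**Not stated there:** the correlation ρ among repeated measurements and the nonsphericity factor ε. Both are assumptions below.

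**1. Reproducing the base size of 20 per group.** For the within-between interaction in a repeated-measures ANOVA:

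- λ = f²·N·m·ε/(1 − ρ)
- df1 = (4 − 1)(5 − 1)·ε
- df2 = (N − 4)(5 − 1)·ε

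With ρ = 0.5, ε = 1 and N = 80: λ = 0.0225 × 80 × 5/0.5 = 18.0, df 12 and 304, power 0.802. With N = 76 (19 per group), power is 0.775. So 20 per group is the smallest equal group size that reaches 80% under these assumptions, and the base size is reproduced.

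**2. Reproducing the 24.** The article does not show its inflation formula.

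- 20 × (1 + 0.20) = 24 per group, 96 in total: matches the stated figures.
- 20/(1 − 0.20) = 25 per group, 100 in total: does not match.

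**3. What 24 per group delivers.**

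- At 20% loss: 24 × 0.80 = 19.2 per group; 96 × 0.80 = 76.8 in total, against 20 and 80 required.
- Largest loss that still leaves 20: 1 − 20/24 = 16.7%.
- Gap in enrolment: 100 − 96 = 4 patients.

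**4. Consequence for power, conditional on ρ and ε.** This treats the analysis as resting on 76.8 patients instead of 80.

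| ρ | ε | Power at N = 80 | Power at N = 76.8 | Gives 20 per group? |
|---|---|---|---|---|
| 0.5 | 1 | 0.802 | 0.780 | yes |
| 0.6 | 0.75 | 0.818 | 0.798 | yes (0.793 at N = 76) |
| 0.3 | 1 | 0.620 | 0.597 | no (28 per group) |
| 0.7 | 1 | 0.972 | 0.965 | no (13 per group) |

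The first two rows are both compatible with the published 20 per group, so the article does not identify one power figure. Across all four rows the loss from the dropout step is between about 0.7 and 2.3 percentage points.

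Steps 2 and 3 do not depend on ρ or ε.

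**The case against.** Four points can be made in the plan's defence.

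- **Dropouts are not all lost.** Statistical analysis specifies intention to treat with multiple imputation, and Data collection and management keeps data already obtained from patients who withdraw, if they consent. Partial data may therefore soften the power loss, and 76.8 complete cases is a pessimistic reading. This stands as a qualification, but it does not reconcile the numbers. The sample size section itself plans for loss and sets 20 as the number needed after it. Dropout criteria says that those who refuse the intervention or do not complete assessments are excluded, and imputation does not recover all the missing information.
- **The gap is tiny.** It is one patient per group on enrolment, in what the Abstract calls a pilot study. This is true, and it limits the weight of the point.
- **Nothing can be changed now.** Trial status reports that recruitment was completed in June 2019. That rules out more patients, but not a correct statement of what 96 allows for.
- **The power figures rest on unstated inputs.** This is right. A reader might infer that the calculation cleared 80% by only 0.2 points, so that there was no slack, and that power at 20% dropout is 78%. The article does not support that as a fact about the authors' test. Both statements hold for ρ = 0.5 and ε = 1, but ρ = 0.6 with ε = 0.75 leads to the same 20 per group with a margin of 1.8 points.

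**Conclusion.** The stated enrolment does not provide the stated dropout allowance. Allowing for 20% loss takes 25 per group (100 in total); 24 per group (96) allows for 16.7%. This follows from the section's own figures and needs no further assumption.

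The practical effect is small: four patients in total and about two points of power. Under the two assumption sets that reproduce 20 per group, power falls from about 80% to about 78%, or from about 82% to just under 80%. These figures are conditional, and data kept from dropouts may reduce the loss. The slip biases no estimate or test, and it does not make the base size of 20 per group wrong.

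**What to change.** Replace the dropout sentence in Sample size estimation, or correct it in the results report, along these lines: *24 per group (96 in total) allows for a dropout of 16.7%; at 20% dropout about 77 patients are expected to be evaluable, slightly fewer than the 80 required.*

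If a power figure is added, give the correlation and the nonsphericity correction that were entered in the software. Without them, no single power value can be derived from the article.

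The cost is one sentence and a slightly less favourable statement. No patients, visits or analyses change.

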### Patient recruitment

Patients will be invited to participate in the research study by notices in local and regional media and by calls for participation to staff members and students at the Hannover Medical School. Semi-structured telephone interviews and subsequent physical examinations will be performed to select patients with frequent episodic or chronic tension-type headaches according to the diagnostic criteria of the International Classification of Headache Disorders, 3rd Edition (IHS 2.2 and IHS 2.3).

After the telephone screening by two scientific assistants, a potential participant is registered and given an initial appointment, which includes a preliminary medical examination, checking of the inclusion and exclusion criteria, collecting comprehensive information, and providing consent to participate. After this appointment and consent to participate in the study, the subject draws one of the previously created opaque randomization envelopes, is assigned to the corresponding group, and is given dates for appointments for the intervention and for follow-up appointments. The appointments and schedules of the patients enrolled in the study are generated by a study nurse who is neither involved in the treatment nor in the randomization. Randomization will be overseen by one of the trial directors.

The total study period for each participant will be 7 months (Figs. 1 and 2). This period includes a 4-week baseline period, a 6-week intervention period, and a 20-week follow-up period. During the intervention period, the subjects in the trial groups will receive a total of 12 treatment units in decreasing frequency (three units per week during the first 2 weeks, two units per week during the third and fourth weeks, and one unit per week during the last 2 weeks). During the entire study period, as-needed analgesics (e.g. ibuprofen, aspirin, and paracetamol) can be taken as usual and will be documented in a headache diary.

**Fig. 1 Fig1:**
[figure not shown]
CONSORT flowchart [18]

**Fig. 2 Fig2:**
[figure not shown]
SPIRIT figure of enrolment, interventions, and assessments. GAD-7 Seven-item Generalized Anxiety Disorder Questionnaire, HRV Heart rate variability, MIDAS Migraine Disability Assessment, PHQ-D Patient Health Questionnaire, Depression, SF-12 12-item Short Form Health Survey

### Inclusion criteria

To be eligible, patients must be aged between 18 and 65 years and have suffered from frequent episodic or chronic tension-type headaches for more than 6 months. An episode of headache must have occurred on at least 1 day per month for at least 3 months, the duration of which must be at least 30 min but no longer than 7 days continuously. Furthermore, subjects must be capable of fully completing all assessments.

### Exclusion criteria

Those who fulfill any of the following criteria will be excluded:
Those participating or having participated during the last 30 days prior to the initial screening examination in another clinical trialThose who have been treated with acupuncture or MTT for tension-type headaches within the last 6 months prior to the initial examinationThose with a serious psychiatric disorderThose with substance dependence or misuseThose using headache medication for >10 days per monthThose with a severe neurological or severe medical diseasePregnant womenNursing womenWomen planning to become pregnant during the study periodThose with migraine whose attacks occur more frequently than once per yearThose with unstable angina pectorisThose with New York Heart Association functional classification III–IV heart failureThose with uncontrollable or untreatable arterial hypertensionThose suffering from headaches due to other medical causes (e.g. pseudotumor cerebri, sleep apnea syndrome, or newly developed daily headaches)

### Dropout criteria

Subjects who refuse to undergo the assigned intervention and those who fail to complete the assessments will be excluded. The close patient contact due to the two or three intervention sessions per week is expected to promote patient adherence and minimize the dropout rate. In addition, we will personally remind the study participants by telephone before each follow-up appointment.

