### Data collection and management

All medical information will be documented and stored separately from personally identifiable data. The data will be recorded on the paper version of case report forms and double entered into a database by outcome assessors. The data sheets will be coded, and the group allocation will not be visible to third parties. Only pseudonymized data will be used for analysis and only members of the study group will be allowed to access these data to preserve patient confidentiality. The acupuncturist, physiotherapists, and statisticians will not have access to these data during patient evaluations. Independent data monitoring is performed by a scientist (JB) who is not involved in the study process. If subjects withdraw from the study, no further data will be collected from them. Data already obtained will be used in the intention-to-treat analysis with the consent of the patient or otherwise completely deleted from the database.

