### Statistical analysis

Descriptive statistics will be used to describe the study population. The comparability of the study groups regarding age, gender, and outcome characteristics will be determined using an analysis of variation (ANOVA) or chi-squared tests. A significance level of *p* < 0.05 will be used for all tests. Analyses will be performed on an intention-to-treat basis. Multiple imputation will be used to handle missing data. To test the primary hypothesis, potential interaction effects (time × intervention) with pain as the primary endpoint will be calculated using a repeated-measures ANOVA. Supplementary Bonferroni-corrected post hoc tests will assess potential intragroup effects. Secondary interval-scale outcome measures will be analyzed using the same strategy. The proportion of treatment responders (those with at least a 50% reduction in the frequency of pain episodes) will be determined in supplementary analyses for the various treatment arms.

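### The dropout rule excludes participants who refuse their arm or miss assessments, which conflicts with the stated intention-to-treat analysis and multiple imputation

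*Protocol article*

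**What the plan says.** Four places in the protocol article bear on who is followed and who is analysed.

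- **Dropout criteria:** "Subjects who refuse to undergo the assigned intervention and those who fail to complete the assessments will be excluded". No qualification follows. The rest of that section is about retention.
- **Statistical analysis:** "Analyses will be performed on an intention-to-treat basis. Multiple imputation will be used to handle missing data". The Abstract repeats the intention-to-treat commitment.
- **Data collection and management:** "If subjects withdraw from the study, no further data will be collected from them". The next sentence reads: "Data already obtained will be used in the intention-to-treat analysis with the consent of the patient or otherwise completely deleted from the database".
- **Sample size estimation:** 20 patients per group are needed for the analysis and 24 per group (96 in total) are recruited, on an assumed dropout of 20%.

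The primary endpoint (Primary outcome) is the change in mean pain intensity from T1, before the intervention, to T3, six weeks after it ends.

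**The concern.** Intention-to-treat keeps everyone in the arm to which they were randomised, whatever they did afterwards, and multiple imputation fills in what they did not provide. The dropout rule names exactly the two kinds of participant these principles exist for: those who do not take up the allocation and those with incomplete assessments. Two analysts working from the article could build two different primary analysis sets, each with a sentence to cite.

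Both grounds for exclusion arise after randomisation, and exposure to them differs by arm. The active arms have 12 treatment units in six weeks (Patient recruitment). Training adds 60-minute units and home exercise three times a week (Medical training therapy), and the combination adds acupuncture after each training session. Usual care continues existing treatment (Control group), so there is almost nothing to refuse. The trial also sets out to judge feasibility and acceptance, and people who decline an arm are among the most informative on that question.

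**Working it through.** **Step 1. The plan's own figure.** The documents give f = 0.15, α = 0.05, four groups, five measurements and 80% power. They do not give the correlation between measurements (ρ) or the sphericity correction (ε), so I assume ρ = 0.5 and ε = 1. For the within-between interaction in G*Power:

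- λ = f² × N × m × ε / (1 − ρ) = 0.0225 × 80 × 5 / 0.5 = 18
- df1 = (4 − 1)(5 − 1) = 12; df2 = (80 − 4)(5 − 1) = 304
- power = 0.802

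So 20 per group reproduces under these assumptions. The result is sensitive to them: with N = 80 and ε = 1, power is 0.62 at ρ = 0.3 and 0.972 at ρ = 0.7. With ρ = 0.5 and ε = 0.75 it is 0.705.

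**Step 2. How many participants the rule could reach.** The planned margin is 24 − 20 = 4 per arm, or 16 in total. A literal 20% loss is 0.2 × 24 = 4.8 per arm, or 0.2 × 96 = 19.2 in total.

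**Step 3. The two readings of the rule.**

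| | Excluded from analysis | Excluded from participation only |
|---|---|---|
| Refusers | Not analysed; intention-to-treat is broken | Analysed, but T3 is not collected |
| Incomplete assessments | Not analysed; little is left to impute | Analysed, but later visits are lost |
| Multiple imputation | Nearly redundant | Must supply T3 values that could have been observed |
| Fit with the Statistical analysis section | Contradicts it | Compatible in form, weaker in substance |

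Nothing in the article chooses between the columns. Nor does it say whether one missed item or one diary day counts as failing to complete the assessments.

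**Step 4. Power under each reading.** With ρ = 0.5 and ε = 1, analysing all 96 gives power 0.885. This is an upper bound, because it ignores information lost to missing values. Analysing 76 (19 per group) gives 0.775. At ρ = 0.3 the pair is 0.724 and 0.591; at ρ = 0.7 it is 0.992 and 0.963. These figures show that the choice of reading matters; they do not decide which one is meant.

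**Step 5. Bias under the first reading.** In an arm, let p be the share excluded and d the mean improvement of those retained minus that of those excluded. Then:

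- retained mean − full-arm mean = p × d
- shift in the contrast, active minus control = p_A × d_A − p_C × d_C

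The documents give none of the arm-specific p or d values. Assume d = 1 to 2 points on the pain scale in both arms:

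- p_A = 0.1 to 0.2, p_C = 0: shift from 0.1 × 1 = 0.1 to 0.2 × 2 = 0.4, favouring the active arm
- p_A = p_C = 0.2: shift 0
- p_A = 0.1, p_C = 0.2: shift from −0.1 × 1 = −0.1 to −0.1 × 2 = −0.2, favouring control

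The sign depends on which arm loses more people, which the article does not tell us.

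**The case against.** The strongest reply is that the sentence sits under a heading about dropout, in a section otherwise devoted to retention, and names no analysis set. Every place that does say who is analysed (Abstract, Data collection and management, Statistical analysis) says intention-to-treat. For people who withdraw, the article adds: "Data already obtained will be used in the intention-to-treat analysis with the consent of the patient". On this view the dropout rule defines who stops taking part, the data section keeps what they gave, and imputation supplies the rest. An analysis plan that is not shown may spell this out.

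Part of this stands. The texts can be read together, so a reader who infers that the primary analysis will certainly be restricted to adherent completers, with nobody left to impute, goes further than the documents allow. Raising 20 to 24 per group does not prove it either, because trials analysed by intention-to-treat routinely recruit extra patients to offset lost information.

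The reply does not remove the conflict. The data section speaks of subjects who withdraw, not of subjects the team excludes. No passage limits the exclusion to treatment or visits, and the Exclusion criteria use the same verb for people kept out of the trial altogether. Even on the kinder reading, follow-up ends for someone who declines sessions but would still keep a diary. An analysis plan can settle the analysis set; it cannot recover T3 values that were never collected.

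A reader might also infer that the rule favours the active arms, most of all the combination, by 0.1 to 0.4 points. The documents do not support that. The figure needs almost no exclusions in usual care and a gap of 1 to 2 points that appears nowhere in the article. Missed assessments can occur in every arm, and the article itself expects frequent session contact to limit dropout. Usual care lacks that contact and could lose more people.

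**Conclusion.** The concern holds as a conflict between stated rules, not as missing detail. Read one way, the dropout rule overrides intention-to-treat; read the other, it ends follow-up early and makes the primary comparison depend on imputation that could have been avoided. Between 16 and 19 of 96 participants are affected if dropout matches the plan's allowance. The refusal ground falls mainly on the active arms, but the net direction and size of the bias are undetermined. The conclusion rests on the wording alone; the power figures depend on the assumed ρ and ε, and the bias figures on assumed values of p and d. It should be settled before the data are analysed, because choosing the analysis set after seeing results would compromise the primary comparison.

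**What to change.** Replace the sentence in Dropout criteria with wording such as:

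> Participants who decline or stop the assigned intervention, or who miss an assessment, remain in the trial. They continue follow-up unless they withdraw consent to it, and are analysed in their randomised arm. Missing values are handled by multiple imputation.

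This concerns follow-up and analysis only and changes nobody's treatment.

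Reconcile Data collection and management with it. Distinguish stopping the intervention from withdrawing consent to data collection. The clause that deletes data when consent is not given is a second route out of the intention-to-treat set, so the number of such deletions should be reported for each arm. Any completer analysis should be labelled as a sensitivity analysis only.

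The Trial status section says recruitment ended in June 2019 and the study finishes in January 2020, so continued follow-up may no longer be possible for some or all who stopped. In that case, fix the analysis-set wording before the data are analysed.

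The cost is wording, keeping the existing reminder calls and diaries going for people who stop the intervention, and possibly a slightly smaller estimate.
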